## Abstract

**Background:**

The two most common interventions for Posttraumatic Stress Disorder (PTSD) are pharmacological treatment with SSRIs such as paroxetine and psychological treatment such as Trauma-Focused Cognitive Behavioral Therapy (TF-CBT). International guidelines recommend trauma-focused psychological interventions for all PTSD patients as first-line treatment (NICE). However, no clear-cut evidence is available to support this recommendation.

**Methods/design:**

In order to compare pharmacological treatment (paroxetine) and psychological treatment (TF-CBT) in (cost-) effectiveness on the short and the long term, we will randomize 90 patients with chronic PTSD to either paroxetine (24 weeks) or TF-CBT (10–12 weeks). We will assess symptom severity and costs before and after the intervention with the Clinician Administered PTSD Scale (CAPS), the Clinical Global Impression Scale (CGI) and the Trimbos/iMTA questionnaire for Costs associated with Psychiatric Illness (TiC-P).

**Discussion:**

This study is unique for its direct comparison of the most commonly used psychological intervention (TF-CBT) and pharmacological intervention (paroxetine) on (cost-) effectiveness on the short and the long term. The anticipated results will provide relevant evidence concerning long-term effects and relapse rates and will be beneficial in reducing societal costs. It may also provide information on who may benefit most from which type of intervention. Some methodological issues will be discussed.

**Trial Registration:**

Dutch Trial registration: NTR2235

## Background

Approximately 80% of the Dutch population experiences at least one traumatic event during lifetime [1]. The risk for development of PTSD after psychological trauma is approximately 10% in the Netherlands [1] as well as in other countries like the US [2]. Higher rates in women than in men have been found in the general population, e.g. 12% versus 4.6% [1,3-5]. PTSD generally continues for long periods of time, with a median time to recovery in the range of 3 to 5 years [2]. The high chronicity, severity, and co morbidity of PTSD are associated with high levels of functional and psychosocial disability [6], but also with high health care costs and economic impact due to health care utilization and negative effect on personal income [7]. Several effective treatments, however, are available to reduce symptoms and lower these costs.

At present, pharmacological treatment with selective serotonin reuptake inhibitors (SSRIs) and psychological treatment with trauma-focused behavioral therapy, i.e. Trauma-Focused Cognitive Behavioral Therapy (TF-CBT) or Eye Movement Desensitisation and Reprocessing (EMDR) are recommended for treatment of PTSD [8,9]. These recommendations are supported by placebo-controlled trials [10-12] and meta-analyses [13,14], which demonstrate that these psychological treatments are effective in treating PTSD symptoms. Selective serotonin reuptake inhibitors (SSRIs) such as paroxetine [15,16], sertraline [17,18] and fluoxetine [19-21] have shown favorable results in placebo-controlled randomized clinical trials. The effectiveness of these SSRIs has also been confirmed in a meta-analysis [22] and supported by reviews [23,24]. Notwithstanding the evidence coming from these guidelines and clinical trials, the choice of treatment in common clinical practice is rather arbitrary and seems to partly depend on indirect and direct assumptions of the clinician, style of health service delivery and patient factors (e.g. [25]). Mellman et al. [26] estimated that in a community-based sample, 77% of the PTSD patients received pharmacotherapy. The preference for pharmacotherapy may be due to the relatively poorer availability and accessibility of trauma-focused behavioral therapy, because of more time-consuming procedures such as referral, waiting list problems and the short handedness of behavior therapists. Little is known, however, about the difference in effectiveness between pharmacological versus psychological treatments.

The only meta-analysis that systematically compared effect sizes of both psychotherapeutic and pharmacological treatments for PTSD showed a slight advantage of CBT compared to other treatments on observer-related total PTSD symptoms [27]. Caution is, however, required when comparing effect sizes of pharmacological to psychotherapy trials as in pharmacological trials with placebo comparison control, non-specific attentional effects may have a more modest impact than in psychological therapy trials with waiting list controls [9]. Some studies compared the effectiveness of pharmacotherapy and trauma-focused therapy directly, suggesting a better long-term outcome for trauma-focused therapy than pharmacotherapy. One study [28] found relapse of PTSD symptoms at 6 months follow-up in the paroxetine group but not in the CBT group, and another study [11] revealed 58% asymptomatic patients 6 months after the trauma-focused psychological therapy group, compared to none in the SSRI group. However, these studies are rather small (respectively N=21 and N=88) and long-term consolidation of more than 6 months follow-up of the effects of pharmacological treatment were not yet reported. Therefore, several important questions regarding effectiveness, duration of treatment and relapse rates remain unanswered. Placebo-controlled studies that investigated treatment duration indicate beneficial effects of more sustained treatment. Martenyi et al. [29] have found a 16.1% relapse rate in 12-week fluoxetine treatment, compared to 5.8% in 24-week fluoxetine treatment. Furthermore, a study of Londborg et al. [30] showed that more than half of 41% non-responders after short-term treatment of 12 weeks achieved responder status during prolonged treatment of at least 24 weeks with SSRIs. Other studies have shown that treatment continuation for more than 24 weeks does not further reduce the PTSD symptoms but yields lower relapse rates than placebo [31,32]. These findings support the notion that a short-term course of treatment with SSRIs may be inadequate [33].

The importance of an adequately powered and designed trial determining whether trauma-focused psychological interventions differ from pharmacological interventions in terms of effectiveness and cost-effectiveness was already emphasized by national and international guidelines [8,9]. Gaining more knowledge on treatments and the consolidation of treatment effects will not only be beneficial for PTSD patients but may also reduce societal costs. Therefore we will compare pharmacological treatment with paroxetine and psychological treatment with TF-CBT in PTSD. We choose to compare these particular treatments as up to now, the majority of the empirical literature on psychotherapies for PTSD has focused on TF-CBT and this is repeatedly shown to be effective (e.g. [14,34,35]). Furthermore, particularly the SSRI paroxetine has proven to be effective in the reduction of symptoms from all three PTSD symptom clusters: re-experiencing, hyperarousal and avoidance [15,16] and has shown to be more effective than sertraline and fluoxetine in reducing PTSD symptom severity [23].

### Research aims and hypotheses

The aim of the proposed study is to compare the effectiveness and cost-effectiveness of Trauma-Focused Cognitive Behavioral Therapy (TF-CBT) to paroxetine in patients with PTSD in a randomized controlled trial in terms of PTSD symptom reduction. Secondary outcome measures include general measures of psychological wellbeing (i.e. anxiety and depression), quality of life, and related costs. Furthermore, we will take into account treatment responses by gender, age, and socio-economic status (incl. ethnic and cultural background) as previous studies show that women are twice as likely as men to develop PTSD during their lifetime [2] and indicate that different psychobiological mechanisms may play a role in the development of PTSD in women compared to men [5].

Based on previous findings of the effects of both treatments on clinical symptomatology over time, we expect the TF-CBT treatment to be more effective in PTSD symptom reduction than paroxetine most prominently at long-term follow-up, i.e. several months or years after cessation of both treatments. Furthermore, we hypothesize that CBT will be cost-effective, especially related to less expected relapse rates in comparison with pharmacological treatment. We will take into account direct medical costs (health care utilization as well as to inpatient and outpatient mental health care, day-treatment and primary physician care), direct non-medical costs (travel to and from health care providers, out-of-pocket costs) and indirect costs (lost productivity due to sick leave).

## Methods/design

The study is funded by the Netherlands Organization for Health Research and Development (ZonMw, grant no. 80-82310-98-09034). The study has been approved by the medical ethical board of the Academic Medical Center (AMC) (registration no: 09/080) and is conducted in accordance with the principles of the Declaration of Helsinki. The trial has been registered in the Dutch trial register and can be found at http://www.trialregister.nl (NTR2235).

### Study design

The study is designed as a randomized controlled trial comparing TF-CBT and paroxetine treatment. The randomization and allocation procedure will be performed by a researcher who has no further role in data collection. The study design was set up with one pre-treatment assessment and four post-treatment assessments (at 1 week, 6 months, 12 months and 18 months) but before starting data-collection the authors added an assessment at 3 months as well (see Figure 1). All assessments will be performed by research workers blinded for the allocated treatment. The study will be performed at the department of psychiatry of the Academic Medical Center (AMC) in Amsterdam. Patients will be recruited over the course of 3 years, starting November 2009.

**Figure 1 F1:**
[figure not shown]
Flowchart.

### Participants

Our study population will consist of patients with PTSD that are referred to the outpatient psychiatric clinic of the AMC. Inclusion criteria are: patients that fulfill all criteria for a diagnosis of chronic PTSD based on the DSM-IV [36], have a score of 45 or higher on the Clinician Administered PTSD Scale (CAPS [37]) 18 years of age or older, give written informed consent and are eligible for exposure therapy. Exclusion criteria are: suicidal risk; presence of any of the following DSM-IV diagnoses: psychotic disorder incl. schizophrenia, a bipolar disorder, depression with psychotic features, or excessive substance related disorder over the past 2 months, a primary diagnosis of severe depressive disorder; an organic disorder that interferes with either TF-CBT or paroxetine treatment; intolerance to paroxetine or any other SSRI; taking psychotropic medications that interact with paroxetine or no mastery of Dutch, English, Turkish or Arabic. Furthermore, female patients of childbearing potential must have a negative pregnancy test. Patients will receive a reimbursement that acknowledges the participants’ time and effort (15€ for each measurement as well as travel expenses).

### Sample Size

#### Sample size calculation

To compare the effectiveness of both interventions, the difference in CAPS scores between the two groups will be analyzed. We expect differences in effectiveness and cost-effectiveness between both treatments to be most prominent at follow-up, i.e. 6 months, 12 and 18 months after cessation of the 12-week treatment periods and therefore sample size calculations should ideally be based on expected differences at follow-up. However, due to very few data available for long-term power calculations, we initially choose to be conservative in our sample size calculation. Based on an earlier RCT on the efficacy of CBT and another RCT on the efficacy of paroxetine in the treatment of PTSD, we expect to find a total CAPS score of 23.7 (SD=26.1) in the cognitive behavioral group [38] and of 34.8 points (SD=25.7) in the paroxetine group [15]. Power calculations showed that a total of 89 participants in each treatment group will be required to demonstrate a difference of 11.1 points (alpha=5%, power=80%). To allow for 20% attrition at follow-up, we will assess 234 patients (N=117 in each treatment group).

#### Sample size calculation adjustment

We decided to adjust the sample size calculation and to optimize the power of the trial given the current study design, resulting in a smaller but more feasible sample size, in the light of possible slow recruitment. The original sample size calculation was based on the outcome on a single follow-up measurement, and was therefore rather conservative. As repeated measurements during follow-up provide additional data, differences can be estimated with higher accuracy, and therefore a smaller sample size is required to demonstrate a similar difference.

The increase in power does not solely depend on the number of measurements, but also on the correlation between measurements on the same patient (intra class correlation or ICC). Additional measurements add relatively less information to previous measurements if measurements are highly correlated. The required sample size for our study was therefore based on the study of Rochon [39] showing that for five measurements on each patient, for ICCs from 0 to 0.5, between 36 and 68 patients are required in each arm with an effect size of Cohen’s *d*=0.3, while between 14 and 25 patients per arm are needed with an effect size of 0.5. With an anticipated effect size of 0.46 we would need between 20 and 36 (depending on the actual ICC) patients per measurement per arm, respectively to gain a difference of 12 points on the CAPS at 18 months post-treatment. Anticipating possible attrition of study participants of 20%, we aim for 45 patients in each arm for the entire study period. Our new sample size is in line with another comparative study on long-term treatment effects of SSRI versus trauma-focused psychological treatment up to date that indicates that a smaller sample size may be sufficient to demonstrate a difference at 6-month follow-up [11].

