### Statistical analyses

All analyses will be performed according to the intention-to-treat (ITT) principle. Patients will be classified as responders and non-responders to treatment. Criteria for treatment response will be a 30% or greater change from baseline on the CAPS and a final CGI rating of 1 or 2 (“much improved” or “very much improved”).

Patients will also be classified in terms of compliance with the treatment regime and completion of the treatment and study procedures. Completers are those patients who finished the study scheme and who were available for at least one post-intervention assessment. Compliance concerns the adherence of treatment protocol, i.e. taking medication. Non-compliant patients are those patients who failed to take their medications or who failed to adhere to the TF-CBT sessions for >25% of the time. Regarding drop-out and loss to follow-up, a careful procedure will be followed in order to avoid an early exclusion of non-completers. Furthermore, adequate methods for imputation of missing data will be used, such as Maximum Likelihood Estimation (MLE) or Multiple Imputation method (MI).

Descriptive statistics will be used to examine differences in demographic, trauma-related characteristics at baseline between the TF-CBT group and the paroxetine group. Continuous CAPS scores at post-intervention assessments will be compared using analysis of covariance with study treatment (SSRI or TF-CBT) as main effect, adjusting for differences at baseline and other potential confounders (i.e. gender, age). Differences between both treatment groups will be evaluated by analysis of repeated measures, using linear mixed models. In multivariate analyses we will adjust the estimated differences for potential confounding variables (i.e. gender, age, SES, co-existence of a moderate depression). Regarding drop-out and loss to follow-up, different analytical approaches (complete case analysis, last observation carried forward, multiple imputation, best/worst outcome) will be followed in order to assess their impact on the study results. All analyses will be performed using SPSS 18.0.

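### The reduced sample size applies a 12-point CAPS difference placed at 18 months as if it were the average over five measurements, while the plan expects the difference to be largest only from 6 months on

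*Protocol article*

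**What the plan says.** The section Sample size calculation takes SDs of 26.1 and 25.7, alpha 5% and power 80%, and arrives at 89 per group (117 with attrition) for 11.1 points at a single assessment. The section Sample size calculation adjustment replaces this with a repeated-measures argument. It cites a published source "showing that for five measurements on each patient, for ICCs from 0 to 0.5, between 36 and 68 patients are required in each arm" at d=0.3, and 14 to 25 per arm at d=0.5. It then states: "With an anticipated effect size of 0.46 we would need between 20 and 36 (depending on the actual ICC) patients per measurement per arm", which it describes as enough "to gain a difference of 12 points on the CAPS at 18 months post-treatment". Allowing for 20% attrition, it settles on 45 per arm.

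On timing, Sample size calculation says: "We expect differences in effectiveness and cost-effectiveness between both treatments to be most prominent at follow-up, i.e. 6 months, 12 and 18 months". Research aims and hypotheses expects TF-CBT to be "more effective in PTSD symptom reduction than paroxetine most prominently at long-term follow-up". The post-treatment visits are T1 (1 week), T2 (3 months), T3 (6 months), T4 (12 months) and T5 (18 months).

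On analysis, Statistical analyses says: "Differences between both treatment groups will be evaluated by analysis of repeated measures, using linear mixed models". It also plans analysis of covariance of post-intervention CAPS adjusted for baseline. It does not name the mixed-model contrast.

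**The concern.** Repeated measurements reduce the variance of an average over visits. They buy power at d=0.46 only if that average is itself about 0.46 SD. The article takes a difference it locates at the last visit and claims for it the precision of all five measurements. This needs a roughly constant effect, which the article neither states nor defends, and which sits awkwardly with its own expectation of a difference that is largest from 6 months on.

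If the difference is smaller at T1 and T2, a comparison averaged over T1 to T5 gives 2/5 = 40% of its weight to visits where the main effect is not expected. A real late advantage could then be missed, while Strengths and limitations describes the sample as sufficient over the short and the long term.

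**Working it through.** **Inputs.** From the two sample size sections: SDs 26.1 and 25.7 (pooled 25.9), 12 points, d=0.46, five measurements, ICC 0 to 0.5, 36 evaluable per arm, alpha 5%, power 80%. Alpha and power come from the first calculation and are not restated in the adjustment; a two-sided test is assumed. The differences at T1 and T2 are assumptions.

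**The plan's own figures.** 12/25.9 = 0.463 and 36/0.8 = 45, so the effect size and the attrition step reproduce. The range 20 to 36 does not. With n = 2(1.96+0.84)²/d² × f and f = (1+(m−1)ICC)/m, d=0.46 and m=5 give 74.2 × 0.2 = 15 at ICC 0 and 74.2 × 0.6 = 45 at ICC 0.5. An autoregressive structure gives 15–16 to 32–35. Scaling the cited figures by 1/d² gives 36 × (0.3/0.46)² = 15 to 68 × (0.3/0.46)² = 29 from the d=0.3 pair, and 17 to 30 from the d=0.5 pair. So 20 to 36 is not too small against the cited source, but its correlation structure cannot be recovered. Under compound symmetry the top of the cited range (68 and 25) corresponds to ICC of about 0.24, not 0.5; both are carried below. Each of these calculations uses one d for the average of the measurements.

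**Power formula.** Noncentral t, df=70, noncentrality = (mean difference/26.1) × √(18/f). With baseline adjusted at r=0.5, f is reduced by 0.25.

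**18 months alone.** f=1: noncentrality 0.460 × √18 = 1.95, power 49%. Adjusted, f=0.75: 2.25, power 60%.

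**Average over T1–T5.** f = 0.2, 0.392 and 0.6 at ICC 0, 0.24 and 0.5; 0.35 at ICC 0.5 adjusted. Example: 6 points early gives a mean of (6+6+12+12+12)/5 = 9.6, and at ICC 0.5 noncentrality (9.6/26.1) × √30 = 2.01, power 51%.

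| Difference at T1–T5 | Mean | ICC 0 | ICC 0.24 | ICC 0.5 | ICC 0.5, adjusted |
|---|---|---|---|---|---|
| 12 throughout | 12.0 | 99% | 87% | 70% | 90% |
| 11.1, 11.1, 12, 12, 12 | 11.64 | 99% | 85% | 67% | 88% |
| 6, 6, 12, 12, 12 | 9.6 | 93% | 69% | 51% | 74% |
| 6, 7, 8, 10, 12 | 8.6 | 87% | 60% | 43% | 64% |
| 0, 0, 12, 12, 12 | 7.2 | 73% | 45% | 32% | 50% |

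**A check that needs no chosen ICC.** Set f so that 36 per arm gives exactly 80% at d=0.46 (f=0.485). Power is then 78% with 11.1 points early, 61% with 6 and 39% with none.

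**Average over T3–T5.** f = 0.333, 0.493 and 0.667; 0.417 adjusted.

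| Difference at T3–T5 | Mean | ICC 0 | ICC 0.24 | ICC 0.5 | ICC 0.5, adjusted |
|---|---|---|---|---|---|
| 12, 12, 12 | 12 | 92% | 78% | 65% | 85% |
| 8, 10, 12 | 10 | 79% | 63% | 50% | 70% |

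**The case against.** A reader might infer that the plan assumes exactly 12 points at every visit, expects little early on, and so falls well short of 80% power. The article does not support that.

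- Most prominent is a ranking. It does not say the early difference is small. The first calculation uses 11.1 points in place of a long-term figure and calls this conservative, which is compatible with a sizeable early difference. With 11.1 points at T1 and T2, dilution costs at most about 3 points of power. This stands. Against it, the 11.1 points come from two separate trials and are not said to be the expected T1 difference, and on that reading the long-term advantage would exceed the early one by only 0.9 points.
- The shortfall depends on the ICC. At ICC 0, 6 points early still gives 93%. At ICC 0.5, a constant effect already gives only 70%, so that part comes from correlation, not timing. Baseline adjustment, which the plan foresees, raises the figures. This stands too.
- No pooled five-visit test is fixed, and a condensed article may leave the contrast to an analysis plan. The missing contrast is therefore not a fault in itself. But the calculation as printed fits only a test on an average, while the quantity it names is the 18-month difference.
- Five measurements could mean baseline plus four post-treatment visits, as in the design before the 3-month visit was added. That does not help: the expected randomised difference at baseline is zero.

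**Conclusion.** The mismatch is real. The printed justification gives an 18-month difference the precision of five measurements, without the near-constant effect this requires, and the article's own statements on timing make that condition doubtful. For the quantity it names, 12 points at 18 months, 36 evaluable per arm give about 49% power, or about 60% with baseline adjusted at r=0.5, not 80%. If a five-visit average is what is tested, power may fall well short of 80%, but the size of any loss cannot be fixed from the article: across the unadjusted settings shown it runs from 99% to 32%, depending on the early difference and the ICC. These figures rest on SD 26.1, compound symmetry, a two-sided 5% test and assumed early differences.

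**What to change.** Make the main treatment contrast of the mixed model the average difference over T3–T5, estimated from a model that keeps all post-treatment visits, baseline CAPS and a treatment-by-visit term. In Sample size calculation adjustment, restate power for that contrast, with the assumed difference at each visit and the assumed correlation. The T3–T5 table supplies the figures, and both of its profiles should be shown, because the more favourable one assumes the full 12 points already at 6 months. Do not present 45 per arm as giving 80% power for 12 points at 18 months.

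The cost is wording and a less favourable stated power; no patients or visits are added. If the effect is constant, the T3–T5 contrast has about 5 to 9 points less power than the five-visit average. With 6 points early it gains 9 to 14 points at ICC 0.24 and above but nothing at ICC 0 (92% against 93%). With growth from 6 to 12 points it gains 3 to 7 points at ICC 0.24 and above, and loses about 8 at ICC 0. The case for it is that it matches the hypothesis, not that it always has more power.

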### Strengths and limitations

A particular strength of the study is that it is unique in comparing a pharmacological treatment with psychological treatments on the short and the long term. Its sample size is sufficient to differentiate the treatment in effectiveness and cost-effectiveness over the short and the long term, where at present only studies are available that did not take into account long-term effects [11,28].

Some limitations may affect the trial that need to be considered. Firstly, even though we aimed to reduce different influencing factors between pharmacological factors and psychological factors, this is rather difficult as the nature of the two treatments differs. Regarding this difference, the two treatments vary in duration as well as in number and length of the sessions, with pharmacological treatment approximately 24 weeks and psychological treatment consisting of approximately 12 weekly sessions. As we already outlined previously, the length of pharmacological treatment is very essential with possible high relapse rates during short-term treatments [29,31]. Despite these differences, we strived for similarity within the protocols as much as possible; both protocols consist of comparable psycho-education as well as a relapse prevention session. Furthermore, questionnaires will be performed in the same order in both treatment protocols. Other differences intertwined in the nature of both treatments should not be eliminated since the comparison of both treatments should be based on conditions that reflect routine clinical practice in this pragmatic effectiveness trial.

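### The adjusted sample size takes credit for five repeated measurements but states its target as a 12-point CAPS difference at 18 months, where 36 evaluable patients per arm give about 49% power unadjusted

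*Protocol article*

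**What the plan says.** Under Sample size calculation, the protocol article sizes a comparison at one follow-up visit. It expects CAPS means of 23.7 (SD 26.1) with TF-CBT and 34.8 (SD 25.7) with paroxetine, and concludes that "a total of 89 participants in each treatment group will be required to demonstrate a difference of 11.1 points" at 5% alpha and 80% power.

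Under Sample size calculation adjustment, it calls that calculation conservative because it used a single measurement. It argues that repeated measurements raise precision and cites tabulated sizes for five measurements and intraclass correlations (ICC) from 0 to 0.5: 36 to 68 per arm at an effect size of 0.3, and 14 to 25 at 0.5. For its own effect size of 0.46 it gives 20 to 36 per arm, "respectively to gain a difference of 12 points on the CAPS at 18 months post-treatment". Allowing for 20% attrition, it aims for 45 per arm.

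Two other places bear on this. Research aims and hypotheses expects TF-CBT to be superior "most prominently at long-term follow-up, i.e. several months or years after cessation of both treatments". Strengths and limitations says of the trial: "Its sample size is sufficient to differentiate the treatment in effectiveness and cost-effectiveness over the short and the long term".

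**The concern.** The reduction and the target do not belong to the same quantity. A required size that falls as visits are added and rises with the ICC describes a difference pooled over visits. At a single visit, a mixed model with treatment-by-visit terms and complete data gives the between-arm contrast about the precision of a comparison at that visit alone. The text takes the pooled saving and attaches it to a single-visit target.

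The trial's main expectation concerns the long term. If readers believe that 45 per arm was enough to show 12 points at 18 months, they may take a non-significant 18-month result as evidence of no difference, although the study had limited power for it.

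**Working it through.** **Inputs.** SDs 26.1 and 25.7, alpha 5% and power 80% come from Sample size calculation. Five measurements, ICC 0 to 0.5, effect size 0.46, 12 points, 20% attrition and 45 per arm come from the adjustment section. Three things are assumed: a two-sided test (sidedness is not stated), 80% power carried over to the adjusted calculation (not restated there), and the correlation *r* between baseline and 18-month CAPS (not given, so shown as a range). Results are for the t-test unless marked otherwise.

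**1. The plan's own figures.**
- Pooled SD = √[(26.1² + 25.7²)/2] = 25.9. Then 11.1/25.9 = 0.43, which needs 87 per arm (stated 89, close enough).
- 12/25.9 = 0.463, so 0.46 is the 12-point difference on the raw single-visit SD.
- 36/(1 − 0.20) = 45, exact.

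**2. Which contrast do the tabulated sizes fit?** For the mean of *m* = 5 visits with equal correlation, the variance is multiplied by (1 + 4·ICC)/5, which is 0.2, 0.4 and 0.6 at ICC 0, 0.25 and 0.5.

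| Effect size | Stated, ICC 0 to 0.5 | Five-visit mean, ICC 0 | Five-visit mean, ICC 0.5 |
|---|---|---|---|
| 0.3 | 36 to 68 | 36 | 106 |
| 0.5 | 14 to 25 | 14 | 39 |
| 0.46 | 20 to 36 | 16 | 46 |

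The ICC = 0 ends at 0.3 and 0.5 match; the upper ends do not. Correlation that decays between visits (AR(1)), baseline-adjusted and change-score contrasts, six measurements, one-sided tests and 90% power were also tried, and none gives the whole range of 20 to 36. Scaling the stated 0.5 row by (0.5/0.46)² gives 14 × 1.18 = 16.5 and 25 × 1.18 = 29.5, so about 17 to 30. Pooling over visits is therefore inferred, partly from this match and mainly from how the stated sizes depend on visits and ICC.

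**3. Size needed at 18 months alone.** n = 2(1.96 + 0.842)²/0.46² = 74.2 by the normal formula, so 75. The t-test needs 76 evaluable per arm, against the 36 stated.

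**4. Power at 18 months.** Noncentrality is 0.46 × √(n/2)/√(1 − r²). Unadjusted this is 1.95 with 36 per arm and 2.18 with 45.

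| Evaluable per arm | r = 0 (unadjusted) | r = 0.3 | r = 0.5 | r = 0.7 |
|---|---|---|---|---|
| 36 (after 20% loss) | 49% | 52% | 60% | 77% |
| 45 (no loss) | 58% | 62% | 70% | 86% |

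A one-sided 5% test, unadjusted, gives 62% with 36 and 70% with 45 (normal approximation).

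**5. Difference detectable with 80% power.** With 36 per arm the detectable effect size is 0.670. That is 0.670 × 25.9 = 17.3 points unadjusted, and 17.3 × √0.75 = 15.0 points at r = 0.5. The target is 12.

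**6. Correlation needed for the claim.** With 36 per arm, √(1 − r²) must be no larger than 0.46/0.670 = 0.687, so r must be about 0.73. With all 45 retained, the detectable effect size is 0.597, the ratio is 0.46/0.597 = 0.770, and r must be about 0.64.

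**7. The pooled test itself.** With a constant effect of 0.46 at every visit, 36 per arm and equal correlation between visits, power is 86% at ICC 0.25 and 70% at ICC 0.5. With all 45 retained it is 80% at ICC 0.5. It falls if the difference is smaller at the earlier visits.

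**The case against.** The strongest defence has four parts.

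First, the plan does not name the contrast that it powers, and the cited table is not available. This stands: a reader might infer that the plan certainly powers the mean over T1 to T5, but the documents do not establish that. The point does not depend on it, because no form of pooling over post-treatment visits sharpens the contrast at one of them when data are complete.

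Second, the planned analysis adjusts for baseline, so the unadjusted 49% is not the analysis that will be run. This also stands, and it is why the result is a range. A reader might call the trial a coin flip at 18 months. That describes only the unadjusted comparison after full attrition. A correlation of about 0.7 brings power close to 80%, but the document gives no correlation to support that figure.

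Third, a mixed model uses partial data from patients who drop out. It cannot recover more than no loss at all, so the row for 45 per arm is the upper limit. A model without treatment-by-visit terms would carry pooled precision to 18 months, but only by assuming the same difference at every visit, which sits badly with the stated expectation of a larger long-term difference.

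Fourth, that expectation need not mean a steep rise. A reader might assume linear growth from zero and conclude that even the pooled test has very little power. The document states no such shape, and its sample size section names 6, 12 and 18 months together. What can be said is only that smaller early differences lower the pooled power.

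**Conclusion.** The claim that 20 to 36 per arm shows 12 CAPS points at 18 months is not supported by the calculation offered for it. At the planned 36 evaluable per arm, power there is about 49% unadjusted and 52% to 77% for assumed baseline correlations of 0.3 to 0.7. With no attrition it is 58% to 86% over correlations of 0 to 0.7. These figures rest on a two-sided 5% test, an effect size of 0.46 and the document's SDs.

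A reader might go on to infer that the trial is adequately sized for the five-visit mean instead. That cannot simply be substituted: at the document's own upper ICC of 0.5 the pooled test has about 70% power with 36 per arm under equal correlation, although 83% (normal approximation) if the correlation is 0.5 between adjacent visits and decays with distance.

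Nor do the documents support two further readings. The choice of primary contrast need not change, since that is a trade-off for the investigators. The absence of a separate power calculation for cost-effectiveness is no error in a condensed article.

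**What to change.** In Sample size calculation adjustment, remove the statement that 20 to 36 per arm shows 12 points at 18 months. In its place:

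- Name the pooled contrast to which the repeated-measures calculation refers, and give its power with 36 evaluable per arm over the stated ICC range, with the correlation structure and the assumption of a constant effect.
- Beside it, give the 18-month power and detectable difference with their assumed baseline correlation: about 49% and 17 points unadjusted, or about 60% and 15 points at a correlation of 0.5.
- State that the test is two-sided, if it is.

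In Strengths and limitations, qualify the sentence on sufficiency over the short and the long term to agree with these figures.

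The cost is a few sentences. No extra patients are needed and the analysis does not change. The downside is that the published power figures become less favourable.
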